### Statistical methods

Data will be presented as absolute and relative frequencies for categorical variables and using descriptive statistics for continuous variables.

The primary endpoint, occurrence of SSI within 30 days after surgery, will be determined as a rate (number of patients experiencing SSI/number of patients undergoing colorectal surgery). The SSI rate will be determined together with a 95% confidence interval according to Clopper-Pearson.

The SSI rate will be compared to the SSI rates obtained for previous years (pre-implementation phase implementation phase) in an unadjusted manner as well as after adjustment for NNIS risk index. The NNIS risk index will be applied according to the methodology of Swissnoso and is based on ASA score, surgical wound classification and duration of surgery.

Potential risk factors of SSIs will be evaluated in an exploratory manner by measures of association and utilizing logistic regression models.

The sample size in this observational study is based on the expected number of patients undergoing colorectal surgery annually. With approx. 150 patients, the half-width of the 95% confidence interval for the SSI rate will not exceed 6.5% as long as the SSI rate is not greater than 18%.

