**Highlights::**

## Background

SSIs are a common problem in the healthcare system [1]. They lead to an increased mortality and morbidity rate. Apart from the negative impact on patients, SSIs cause high healthcare costs due to prolonged hospital stay and readmission of patients. Colorectal surgery, in particular, is associated with a high infection rate ranging from 15% to 30% [2,3].

In order to understand the causes of SSIs, risk factors have to be evaluated. Intrinsic and extrinsic factors have previously been defined [4]. Intrinsic risk factors are patient-associated and can be subclassified in modifiable and non-modifiable features. Modifiable intrinsic risk factors include diabetes, alcoholism, smoking status, obesity and preoperative albumin level. Examples of non-modifiable risk factors include age and recent radiotherapy. Extrinsic risk factors are procedure-related and involve emergency surgeries or facility risk factors. There are several strategies to prevent SSIs. The biggest impact has been found in the combination of different measures into a bundle of care [5,2,6].

The Cantonal Hospital Lucerne (LUKS) is an 870-bed public acute care teaching hospital serving a population of about 500.000 people in central Switzerland. From October 2016 till September 2017 the rate of SSIs in colorectal surgery in LUKS was 18.1% whereas the average rate of SSIs in Switzerland was 13.7% during the same period of time [7]. These nationwide data were collected and analyzed by Swissnoso, an organization monitoring SSIs cross-disciplinary.

In order to reduce the SSIs at LUKS, we created a colorectal bundle containing 9 measures. These measures were based on a literature research and selected in cooperation with the Department of Hospital Infection Control.

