### Patient population

All patients undergoing colorectal surgery from January 2021 until December 2021, fulfilling the inclusion criteria and having signed an informed consent form will be included in the study. According to our annual case load, we expect to enroll about 150 patients in the study. The data of the patients which are prospectively included in this study will be compared with the data analyzed by Swissnoso (October 2017–September 2018 and October 2018–September 2019). From 2017–2018 153 patients were included and 31 infections were detected (5 superficial, 8 deep and 18 involving the abdominal cavity).

From 2018–2019 after partial implementation of the colorectal bundle actions 126 were included and 15 infections occurred (2 superficial, 4 deep and 9 involving the abdominal cavity). Concerning the three time periods, data acquisition is retrospective for the first two periods and prospective for the final period.

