### Implementation of the colorectal bundle

In our study protocol we defined three time periods in order to evaluate the effectiveness of our colorectal bundle. We collected data and analyzed the SSI rate from October 2018 till September 2019, before our bundle was implemented. From October 2019 till September 2020, a first set of measures was established. Therefore, this time period is defined as “during implementation”. In January 2021 the full extent of our colorectal bundle was implemented and the time period “after implementation” started for one year.

Following measures were defined based on a current literature review.

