#### Pre-implementation phase (October 2018–September 2019)

During this time period, 137 patients underwent colorectal surgery. Only basic measures for preventing SSI were performed:

Hair was removed in the operating field with a clipper instead of a shaver.Blood glucose was monitored only during the operation.Antibiotic prophylaxis was applied 60 minutes before the operation.The application of an antibiotic prophylaxis was repeated if the operation lasted longer than 4 hours.Measures of warming were only applied during the operation and in the recovery room.Instruments and gloves were changed after finishing the anastomosis.

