Our study has some limitations that have to be acknowledged. First of all this is a single-center study. We assume that the bundle will lead to a decrease of SSIs in our institution, but whether our measures can be applied successfully in other institutions, is difficult to predict. Secondly, the value of each individual measure is difficult or impossible to evaluate and this poses a problem in the interpretation of the effects of a whole bundle of care. Thirdly, our study has three periods of implementation of the measures of the colorectal bundle; while two periods were analyzed retrospectively, data of the main study period is acquired prospectively. Lastly, since different measures and combinations of measures are used in different bundles, comparability in literature is limited.

Besides analyzing the effects of our colorectal bundle on SSIs, we aim to investigate the impact of risk factors like smoking habits, alcoholism, weight, etc. and their combination.

This investigation is part of a quality improvement project to reduce SSIs and their consequences for the patients and the whole healthcare system.

Originally the timelines were from October 2020 to September 2021, but due to the Corona pandemic we had to alter the timeline from January 2021 to December 2021.

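### The phase comparison adjusts for case mix but not for calendar time, so it cannot by itself credit a change in SSI rate to the bundle

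*Protocol article*

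**What the plan says.** - **Comparison** (Statistical methods): "The SSI rate will be compared to the SSI rates obtained for previous years", and this is done "in an unadjusted manner as well as after adjustment for NNIS risk index". The same section bases the index on ASA score, wound classification and operation time. No time term and no outside series is named.
- **Aim** (Abstract, Methods and Discussion): the phases are formed to judge whether the actions work, and the study is to determine whether the bundle brings a significant reduction.
- **National figure** (Background): for October 2016 to September 2017, "the rate of SSIs in colorectal surgery in LUKS was 18.1% whereas the average rate of SSIs in Switzerland was 13.7" per cent. This is the only national rate given, and it is not part of the planned comparison. The Swissnoso data named under Patient population are the hospital's own earlier years.
- **Earlier hospital years** (Patient population): "From 2017–2018 153 patients were included and 31 infections were detected", and "From 2018–2019 after partial implementation of the colorectal bundle actions 126 were included and 15 infections occurred".
- **The same year 2018–19 elsewhere** (Implementation of the colorectal bundle): "We collected data and analyzed the SSI rate from October 2018 till September 2019, before our bundle was implemented". The section on the pre-implementation phase adds: "During this time period, 137 patients underwent colorectal surgery".
- **Limitations** (Discussion): single centre, value of the individual measures, two retrospective periods, and comparability with the literature. Change over time is not listed. The Discussion also says that "due to the Corona pandemic we had to alter the timeline".

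**The concern.** In a before-after study at one hospital, anything that changes with the calendar is mixed with the phase. Examples are a general trend in SSI rates, changes in surveillance or staffing, the pandemic, and chance movement after an unusual year. NNIS adjustment removes differences in three case-mix items and leaves the rest.

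The protocol gives reason to take this seriously. The project was set up after a local rate above the national one, and the Discussion reports rising SSI numbers before it. The hospital's rate then differed by more than 8 points between two adjacent years. At stake is the study's main conclusion: a lower 2021 rate could be read as a bundle effect when it is background change, or background change could mask a real effect.

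**Working it through.** **The plan's own figure.** The precision statement is a 95% half-width of at most 6.5% for about 150 patients and a rate up to 18%. Clopper-Pearson for 27/150 gives 12.2% to 25.1%, half-width 6.44%, so it reproduces. It describes the 2021 rate alone, not a difference between phases.

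**Difference between the two earlier years** (Patient population)
- 2017–18: 31/153 = 20.3% (Clopper-Pearson 14.2 to 27.5).
- 2018–19: 15/126 = 11.9% (6.8 to 18.9).
- Difference: 0.2026 - 0.1190 = 0.0836, or 8.4 points.
- SE = √(0.2026×0.7974/153 + 0.1190×0.8810/126) = 0.0435. The 95% CI is 8.4 ± 1.96×4.35 points, or -0.2 to 16.9.
- Fisher p = 0.075; chi-square p = 0.061.
- If the 137 patients of the pre-implementation section are the right denominator and the same 15 infections apply (an assumption), the rate is 15/137 = 10.9%. The difference is then 9.3 points (1.1 to 17.6), Fisher p = 0.036.

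**Which year is the baseline?**

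| Section | 2017–18 | 2018–19 |
|---|---|---|
| Patient population | comparator, 31/153 | comparator, after partial implementation, 15/126 |
| Implementation of the bundle; pre-implementation phase | not a phase | before the bundle, 137 patients |

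On the first account, part of the fall may be a bundle effect. On the second, the fall precedes every added measure, but 2017–18 then lies outside the three phases.

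**What the comparison would show if 2021 merely matched 2018–19.** Assume 150 patients in 2021, a fixed comparator of 31/153, and a two-sided Fisher test at 0.05 (the article states no test or level).
- 17/150 gives p = 0.041 and 18/150 gives p = 0.061. Significance therefore needs 17/150 (11.3%) or fewer, a fall of 20.3 - 11.3 = 8.9 points before rounding.
- P(X ≤ 17) for X ~ Binomial(150, 0.119) is 0.48.
- The same probability is 0.24 at a true rate of 13.7% (the 2016–17 national rate) and 0.62 at 10.9%.
- At a true rate of 11.9%, the observed 2021 rate would be below 20.3% with probability 0.998.
- Against 15/126 instead, significance needs 7/150 (4.7%) or fewer.

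**Direction of regression to the mean.** With 2017–18 as baseline (20.3%, above the hospital's 18.1% of 2016–17 and the national 13.7%), later rates would tend to fall, which favours the bundle. With 2018–19 as baseline (11.9%, below both), later rates would tend to rise, which could hide an effect.

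**Could a time term in the model solve this?** Assume 126, 140 and 150 patients spread evenly over the three phases (140 is assumed). In a linear approximation, adding linear calendar time to phase multiplies the standard error of the post-implementation effect by about 3.3. The 95% half-width goes from about 8 points to 25 or more. Phase and time are nearly collinear, so such a model would be uninformative.

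**The case against.** The strongest reply has four parts.

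- **The comparison is not crude.** NNIS adjustment is planned and deals with three drivers of change between years. That is correct and should be acknowledged, but it does not reach calendar time.
- **The fall from 20.3% to 11.9% proves nothing about background change.** The section that supplies both rates puts the lower year after partial implementation. On the other timeline, the higher year is not in the phase comparison at all. This stands. A reader might infer that the hospital's rate is known to have dropped without any intervention and that this drop would be credited to the bundle. The documents do not support that: the timing is contradictory, and the interval for the fall includes zero.
- **Regression to the mean need not flatter the bundle.** This also stands. The direction depends on the baseline, and the 18.1% of 2016–17 was followed by a higher rate, not a lower one.
- **This is a single-centre quality-improvement project in a condensed article.** Sensitivity analyses may be described elsewhere. That is a fair reason not to demand a full interrupted time series. But the comparison and its adjustment are stated in the text, as are the causal aim and a list of limitations that omits the point.

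**Conclusion.** The point holds in limited form. The planned comparison controls for case mix only, the stated aim is causal, and the lack of calendar-time control is not acknowledged. Under either choice of baseline, change over time would be credited to the bundle or would mask its effect.

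The size depends on the baseline. Against 31/153, a 2021 rate that had merely stayed at 11.9% would give a significant fall about 48% of the time, assuming 150 patients and a two-sided Fisher test at 0.05. Across assumed true rates of 13.7% to 10.9% the range is 24% to 62%.

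It would go too far to say that the 8.4-point difference is as large as any effect the study could show. It is slightly below the 8.9 points needed for significance against 31/153, and it is compatible with chance. Nor can it be called background change or bundle effect until the sections on patient population and on implementation agree about 2018–19 and about 126 or 137 patients. The pandemic is a plausible further influence, but the article gives nothing with which to size it.

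**What to change.** 1. Reconcile the phase label and the patient count for 2018–19 across the sections, and state which years form the baseline.
2. For each phase, and for 2016–17 and 2017–18 as extra baseline points, report the hospital rate beside the national Swissnoso colorectal rate for the matching period. Standardise by NNIS where such figures can be had.
3. Report the change in the hospital-to-national ratio as a supporting analysis for attribution. The starting value for 2016–17 is 18.1/13.7 = 1.32.
4. Add the lack of calendar-time control to the limitations, including that regression to the mean can act in either direction.
5. Soften the Abstract's causal wording, for example to whether the SSI rate is lower after the bundle than before it.

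Do not add a model with phase plus a linear time term.

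**Cost.** Aggregate figures from a surveillance body whose data and method the study already uses, one table, and a few sentences. The national year cited runs October to September; if later reports follow the same calendar, 2021 spans two of them and matching will be approximate. The article gives only one national rate, so the availability of later ones, and of NNIS-stratified ones in particular, is an assumption.

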**Methods::**

All patients undergoing colorectal surgery between October 2018 and December 2021 will be included in a prospective observational study. Since our colorectal bundle has been established gradually, patients will be grouped in a pre-implementation (2018–2019), implementation (2019–2020) and post implementation phase (2021), in order to assess the effectiveness of the actions undertaken. Primary endpoint of this study will be surgical site infection (SSI) rate, while secondary endpoints encompass potential risk factors for SSIs. We assume that obesity, age, diabetes, alcoholism and smoking may lead to a higher risk for SSIs.

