#### Post-implementation phase (January 2021 – December 2021)

During this phase, additional measures are being implemented.

Close monitoring of blood glucose. During the stay in the recovery room and for 48 hours post-operative, blood glucose is monitored closely. Moreover, if blood glucose is higher than 9 mmol/l, the patient will be treated with insulin. This measure is applied to diabetic as well as to non-diabetic-patients.The measures of warming are intensified. First of all, during the operation and during the stay in the recovery room, patients will be placed on warming mattresses. Moreover, a warming towel will be placed on the operating field directly after the operation.The patients will be asked to take a shower the night before surgery. In case of an emergency operation, patients will be asked to wash the axilla, trunk, genitalia, groins and umbilicus.

The primary endpoint of this study is occurrence of SSI within 30 days after surgery. Evaluation of risk factors for SSI will be secondary endpoints. In ***Table 1***, the patient-associated risk factors and procedure-associated risk factors assessed in our study protocol are listed.

**Table 1 T1:** Questionnaire for SSI Risk factors.

PATIENT ASSOCIATED RISK FACTORS	PROCEDURE ASSOCIATED RISK FACTORS

Age	Date of the operation?

Sex	Duration auf the operation (min)

Diagnosis	What kind of operation was performed?

Weight	Which technique of surgery was done (open, laparoscopic, robotic)?

Fat tissue measured in CT scan	Which type of stoma was inserted?

Height	

BMI	

Diabetes and what kind of diabetes	

HbA1c	

Alcoholism	

Immune-deficiency diseases and which type of disease exactly	

Smoking	

Immunosupressive drugs and which ones	

Chemotherapy	

Radiotherapy	

COPD	

pAVK	

Renal insufficience	

Length of hospitalization	

Pre-Albumin	

ASA Score	

Contamination Class of wounds	

Moreover, we measure pre-albumin levels to determine the nutritional status. We assess whether immune-modulatory supplements like Oral Impact^®^ have been given before surgery. We include the ASA (American Society of Anesthesiologists) score in our data to define the general health status of the patient. Furthermore, we classify the grade of contamination of the wound prior to surgery.

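### Length of hospitalization is listed as an SSI risk factor although the article says SSI prolongs stay, and about 18–27 expected SSIs support only a small joint model of the 27 listed items

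*Protocol article*

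**What the plan says.** The section on the post-implementation phase makes risk-factor evaluation the secondary endpoint and refers to Table 1 for the patient- and procedure-associated factors to be assessed. The table has 22 patient items and 5 procedure items. They include weight, height and BMI as separate entries, "Fat tissue measured in CT scan", and length of hospitalization.

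Statistical methods gives the analysis in one sentence: "Potential risk factors of SSIs will be evaluated in an exploratory manner by measures of association and utilizing logistic regression models". It gives no variable list or model size, and it does not say whether the 2021 patients alone or all phases are used. The Discussion adds an interest in how such factors act in combination.

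The Abstract names five expected factors: "We assume that obesity, age, diabetes, alcoholism and smoking may lead to a higher risk for SSIs". Statistical methods gives these five no priority.

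On direction of effect, the Background says: "SSIs cause high healthcare costs due to prolonged hospital stay and readmission of patients". The Discussion repeats that SSIs increase length of stay.

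On size, Patient population says: "According to our annual case load, we expect to enroll about 150 patients in the study". The only justification of that number concerns the overall SSI rate.

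**The concern.** Length of hospitalization, as listed, is complete only at discharge, so in a patient whose SSI arises in hospital much of it accrues after the infection. The article itself treats longer stay as a consequence of SSI. Testing it as a risk factor would return an association that runs from outcome to exposure. Placing it in a joint model would condition the other factors on something the outcome has changed. Neither a larger sample nor an exploratory label cures this.

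The second issue is capacity. The sample is the annual caseload, checked only for precision of the overall rate. Joint modelling appears to be intended, yet the expected number of infections can carry very few parameters. A large model would give unstable odds ratios and could obscure the five factors that the authors expected to matter.

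**Working it through.** **The plan's own figure.** Statistical methods states: "With approx. 150 patients, the half-width of the 95% confidence interval for the SSI rate will not exceed 6.5" per cent "as long as the SSI rate is not greater than 18" per cent. The method is given as: "The SSI rate will be determined together with a 95% confidence interval according to Clopper-Pearson". For 27 of 150 (18%), the Clopper-Pearson limits are 12.2% and 25.1%, so the half-width is (25.1 − 12.2)/2 ≈ 6.4 points (6.44 unrounded). This is the largest value for 0 to 27 events. The statement reproduces, but it concerns one overall proportion and says nothing about risk-factor models.

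**Inputs**
- n = 150 (Patient population).
- Lower rate about 12%: 15/126 = 11.9% in 2018–2019 (Patient population).
- Upper rate 18%: the planning ceiling (Statistical methods).
- Listed items: 22 + 5 = 27 (Table 1).
- Named factors: 5 (Abstract).

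**Expected events, 2021 cohort only** (events = 150 × rate)

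| SSI rate | Events | Per listed item (÷27) | Per named factor (÷5) |
|---|---|---|---|
| 12% | 18 | 0.67 | 3.6 |
| 18% | 27 | 1.00 | 5.4 |

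At the 2017–2018 rate of 31/153 = 20.3%, there would be 30.4 events: 1.13 per item and 6.1 per named factor. Several items have more than two categories (diagnosis, kind of operation, surgical technique), so the parameters would outnumber the items.

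**How many parameters this supports.** The article sets no criterion. As an assumption, 10 events per parameter allows 18/10 = 1.8 to 27/10 = 2.7 parameters. A laxer 5 per parameter allows 3.6 to 5.4. Even the five named factors are at the edge, which is the reason for penalisation.

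**If earlier periods are pooled (assumption).** With the counts in Patient population, events are 31 + 15 + 18 = 64 to 31 + 15 + 27 = 73, in 153 + 126 + 150 = 429 patients. Per listed item that is 64/27 = 2.4 to 73/27 = 2.7. Per named factor it is 64/5 = 12.8 to 73/5 = 14.6. If two phase terms and one linear NNIS term are added (8 parameters in all), it is 64/8 = 8.0 to 73/8 = 9.1. These pooled figures are uncertain. The article gives both 126 and 137 patients for October 2018–September 2019, and it defines the two earlier periods differently in Patient population and in the section on implementation of the bundle.

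**Single-factor analyses.** Testing 27 items at 5%, if all were null and independent, gives 27 × 0.05 = 1.35 expected false positives and a chance of at least one of 1 − 0.95^27 = 75%. For power, take one binary factor with prevalence 20% or 50% (assumed) and overall SSI rate 12% or 18%. Solve (1 − prevalence) × p0 + prevalence × p1 = rate, with p1 = OR × p0/(1 − p0 + OR × p0), and compare the two proportions in 150 patients. For example, at 12% and prevalence 50%, OR 2 gives p0 = 8.4%, p1 = 15.6% and power 27%. Across the settings, power is 27–36% for OR 2, 54–69% for OR 3 and 71–86% for OR 4.

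**Direction of length of stay.** Table 1 places it among the causes to be assessed, while the Background and the Discussion place it among the effects of SSI. The documents give no figure for the size of the resulting bias, so only its direction can be stated: infected patients stay longer, so long stay will look like a risk factor.

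**The case against.** A reader might infer that all 27 items go into one logistic regression and that the secondary results would be mostly noise. The text does not support this. Table 1 is titled as a questionnaire, and it holds raw inputs and an administrative date. Statistical methods speaks of association measures and of models in the plural, without a variable list. Performance figures for a single 27-term model would therefore describe an analysis that nobody has stated. The analysis is labelled exploratory, so no confirmatory claim rests on it. Model building is also commonly left to a full protocol or analysis plan, which is not shown here. Single-factor analyses have fair power for large effects, though not for moderate ones.

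Two further limits apply. The 18–27 events hold only for the 2021 cohort. The Abstract includes patients from October 2018, and pooling would raise the count. Nor does a smaller joint model remove multiplicity. With length of stay, weight and height dropped and five factors in the model, 27 − 3 − 5 = 19 items remain for univariable reporting. If all are null and independent, the chance that at least one 95% interval excludes no effect is 1 − 0.95^19 = 62%. The exploratory label has to carry that.

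All of this stands, and it confines the capacity point to the size of any joint model. It does not answer the entry for length of hospitalization, which contradicts the article's own account of cause and effect. One might reply that preoperative stay was meant, but the item does not say so.

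**Conclusion.** The point holds in two parts. The firm part is that listing length of hospitalization as a risk factor is wrong as written, and the resulting association would be at least partly reverse-causal. This needs no numerical assumption. The second part is a limit: on 2021 data alone, at SSI rates of 12–18%, there are 0.7–1.0 events per listed item and 3.6–5.4 per named factor. Any joint model well beyond a few factors would be overfitted. If earlier phases are pooled on the Patient population counts, the five-factor model becomes comfortable (12.8–14.6 events per factor before further terms), while a model of all items (2.4–2.7 per item) does not. The overlap of weight, height and BMI is a smaller defect, since BMI is computed from the other two.

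The consequence is modest, because this is a secondary, exploratory analysis and the primary endpoint is unaffected. It is still worth correcting, because it bears on the whole of the stated secondary endpoint and the change is nearly free.

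**What to change.** - Remove length of hospitalization from the risk-factor candidates and report it as a descriptive outcome.
- Use BMI in place of weight, height and BMI together.
- Confine the multivariable model to the five factors named in the Abstract (obesity as BMI, age, diabetes, alcoholism, smoking), fitted by Firth-penalised logistic regression.
- State which cohort is used. Add phase and NNIS risk index to that model only if earlier phases are pooled and the five items are available there.
- Report the remaining items, including CT fat tissue, as univariable estimates with 95% confidence intervals, labelled hypothesis-generating, with no selection by p-value.

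The cost is a few sentences in the analysis plan, with no change to enrolment or to the data collected. The downside is that fewer factors receive a mutually adjusted estimate. Pooling, if chosen, depends on retrieving the items for the retrospective periods and on settling how those periods and their patient counts are defined.
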